**Fig. 1 Fig1:**
[figure not shown]
Overview of events across parallel sub-studies

Sub-study 1 involves four intervention groups: (1) normobaric hypoxia (12% O_2_) combined with cognitive training, (2) hypoxia (12% O_2_) with no training, (3) cognitive training under normoxia (20% O_2_), and (4) normoxia (20%) with no training in a double-blinded controlled design. This design enables us to disentangle combined and separate effects of altitude-like hypoxia and cognitive training. Participants are randomized in blocks and undergo interventions in these groups for practical reasons. During the three-week treatment, participants breathe 12% ambient oxygen (≈ 4400 m altitude) or approximately normal sea-level oxygen (20%) in a treatment room, 3.5 h daily, six days per week (18 sessions in total). After a blood test (days 1, 6, 20) and light standardized breakfast, they enter the treatment room. Here, they sit at a desk separated by desk dividers. On iPads, they perform cognitive training or matched control games without cognitive benefits. Cognitive training is interleaved by short breaks, during which the participants can relax or walk on a treadmill inside the room. This is to avoid complete physical inactivity throughout the 3.5 h sessions and thereby make the sessions more pleasant for participants. Participants undergo cognition assessments in weeks 1 (baseline), 4, and 8 and functional and structural MRI in weeks 1 and 8, when red blood cell counts are comparable between groups. Participants in the two extreme groups (normobaric hypoxia with cognitive training and normoxia with no training) will also undergo PET scanning in week 4 (post-treatment). Participants will be recruited consecutively for the PET scans until an equal distribution in each of the extreme intervention arms (i.e., hypoxia with cognitive training and normoxia with no training), sex, and age group is achieved.

Sub-study 2 involves two intervention groups: (1) normobaric hypoxia (12%) combined with cognitive training 3.5 h daily, five to six days per week for three weeks (16 sessions in total), and (2) treatment as usual (TAU) in an assessor-blind controlled design. Patients in the TAU group will initially be assessed at the same time points as the active group with neurocognitive testing at baseline, week 4, and week 8, fMRI at baseline and week 8, and PET in week 4. After completed testing at week 8, patients in the TAU group undergo the three-week active intervention, followed by one additional neurocognitive assessment and mood rating in the week after treatment completion. The inclusion of this TAU arm rather than an active control group was chosen to ensure patient motivation and minimize attrition in this time-intensive study. Similar study designs with TAU control groups are common in pro-cognitive intervention studies investigating novel treatments in mood disorders and schizophrenia [39, 40]. Although patients will not be blinded to their allocated treatment arm, neurocognitive test results are generally not susceptible to placebo effects [41, 42] and assessments will be carried out by blinded, fully trained research assistants (psychology students).

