### Randomization and blinding

Randomization is conducted in the database program REDCap [51], which is also used to store the collected data, utilizing a 1:1 allocation ratio. Randomization occurs after inclusion of the participants planned to undergo treatment sessions together. Treatment groups are stratified for age (> 27 in sub-study 1 of generally young volunteers/ > 35 in sub-study 2 of patients). For randomization purposes, date of birth is registered to determine the stratum to which the participant belongs at the time of enrolment. Study identification numbers are given consecutively within each stratum and treatment arm. Randomization is conducted in the randomization module in REDCap, where an un-blinded researcher inputs the stratum and the program then retrieves the allocated intervention. To ensure blinding of the outcome-assessors, the randomization module in REDCap is only accessible to the researchers, who are not involved in evaluation of the efficacy parameters.

Healthy participants in sub-study 1 are blind to the oxygen condition since the low/normal oxygen air blown into the room is of equal temperature and humidity. Furthermore, they are told that they receive one of two forms of cognitive training, which effectively blinded participants in a previous study [52]. After study completion, we will assess whether blinding has been maintained for each participant, since there is a small risk that some participants develop symptoms of mild altitude sickness which could unblind them to their intervention. Blinding of the outcome assessors is ensured by their absence during the training visits (where oxygen levels are displayed and monitored on a screen outside the room). Participants will be instructed not to disclose any information concerning their intervention during outcome assessments and under no circumstances will the allocation be revealed to the outcome assessors. The training visits are conducted by researchers who are not involved in outcome assessments.

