### Intervention: hypoxia cognition training

#### Low/normal ambient oxygen

Fresh air with 12% or 20% O_2_ is blown into a sealed 20 m^3^ room by a 4 kW air compressor with a safety-approved system developed by HöhenBalance, Austria (see Fig. 2 for experimental setup). For the active condition, participants enter the room at 16% O_2_ (≈ 2,200 m altitude). Upon entry, the O_2_ levels will be reduced from 16 to 12% (≈ 4400 m altitude) in a 30-min lead-in phase. The precise control by the HöhenBalance systems allows control of O_2_ levels to ± 0.1%. The target O_2_ level of 12% will be maintained over three hours.

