### Sample size and power calculation

Power calculations were performed with the software program G*Power 3.1.9.4 [74] and were based on the primary hypothesis that altitude-like hypoxia combined with cognitive training produces robust sustained cognitive improvement compared with normoxia and no training (hypothesis i). As hypoxia triggers the endogenous production of EPO, we based the power calculation on our previous clinical study of subcutaneous EPO treatment in which we demonstrated clinically relevant cognitive enhancement [75]. In that study, the differential change between EPO and placebo groups in the same cognitive composite score as we apply in the present study was 0.5 standard deviations (SD) [75]. Assuming an effect of 0.4 SD differential change (medium effect size) between the two groups and 0.5 SD of the change, we will achieve > 80% power to detect an effect at an alpha level of 0.05 by including 26 participants per group. This number of participants provides adequate power for the structural and functional MRI investigations based on our previous studies of EPO [30, 32, 33]. To accommodate for up to a 20% drop-out, we will include 30 participants per treatment arm; i.e., 120 participants in sub-study 1 and 60 patients in sub-study 2.

For PET imaging of SV2A [^11^C]UCB-J binding (reflecting presynaptic density), power calculations involved the following assumptions: (i) the average (SD) *BP*_ND_ in the frontal cortex in healthy participants is 3.36 (0.38) (based on in-house data), and (ii) the combined intervention will lead to a 10% increase in *BP*_ND_. With these assumptions, we will achieve a power of 0.82 to detect an effect at significance level of 0.05 post-treatment of the combined intervention (primary aim) with *n* = 20 per treatment arm using a two-tailed, independent-sample *t*-test.

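### The 26 per group gives more than 80% power only if people treated together in one room have uncorrelated outcomes, and the analysis as described names no term for the treatment group

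*Protocol article*

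**What the plan says.** Study design and procedure, on sub-study 1: "Participants are randomized in blocks and undergo interventions in these groups for practical reasons". Randomization and blinding, which covers both sub-studies: "Randomization occurs after inclusion of the participants planned to undergo treatment sessions together". That section also describes a researcher entering the age stratum of a participant and the system returning an allocation, which reads as individual randomisation.

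Low/normal ambient oxygen describes a single installation: air at 12% or 20% oxygen is supplied to a sealed 20 m³ "room by a 4 kW air compressor with a safety-approved system". People in the same session therefore cannot be at different oxygen levels. Sessions last 3.5 hours, 18 times in sub-study 1 and 16 times in sub-study 2.

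Sample size and power calculation sets out its premise as follows: "Assuming an effect of 0.4 SD differential change (medium effect size) between the two groups and 0.5 SD of the change". The conclusion drawn from that premise is that "we will achieve > 80% power to detect an effect at an alpha level of 0.05 by including 26 participants per group". It gives no group size, ICC or design effect. The statistical analysis section describes a mixed model of change over time by arm, tested through the interaction. It lists no random effects, so a session-group term is neither included nor excluded.

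**The concern.** People who spend three weeks together in one room share the calendar period, the supervising staff, the company and whatever goes well or badly in that run. If this makes their changes in cognition more alike, each extra person in a group adds less information than an independent person would. A sample size that counts people as independent then promises more power than the trial has. If the final model also leaves the group out, intervals are too narrow and the type I error exceeds 5%.

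This bears on every contrast that crosses the oxygen conditions, including the comparison that the sample size was built for (hypoxia with training against normoxia without training). In sub-study 2 it bears on active treatment against treatment as usual.

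**Working it through.** **Inputs from the article.** Difference 0.4 and SD of change 0.5, so d = 0.4/0.5 = 0.8; alpha 0.05; 26 per group analysed and 30 enrolled; "utilizing a 1:1 allocation ratio". Sidedness is not stated for the cognitive outcome. I take two-sided, as the article does for PET ("using a two-tailed, independent-sample *t*-test").

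**Assumed, because not given.** Number of people from the same arm sharing a treatment group, m = 4 to 6; ICC of the change score = 0.02 to 0.10. If training and sham participants share a session, m per arm is smaller than the number in the room.

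**Step 1: reproduce the plan.** Noncentrality = d × √(n/2) = 0.8 × √13 = 2.884. With 50 df, power is 80.7%. At n = 25 it is 79.1%. So 26 is the smallest n that reaches 80% in an independent-sample t-test, with no allowance for grouping.

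**Step 2: the margin.** Power falls to 80% when the variance is multiplied by about 1.019. Since DE = 1 + (m − 1) × ICC, this needs an ICC of only 0.0065 at m = 4 or 0.0039 at m = 6.

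**Step 3: both arms clustered (sub-study 1).** Effective n = 26/DE and noncentrality = 2.884/√DE. Individual df = 50; group-level df = 2 × 26/m − 2. Type I error if the group is ignored = 2 × P(T50 > 2.009/√DE).

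| m, ICC | DE | Effective n | Power, 50 df | Power, group df | Type I error if group ignored | n per arm needed (26 × DE) |
|---|---|---|---|---|---|---|
| 4, 0.02 | 1.06 | 24.5 | 78% | 72% (11 df) | 5.7% | 28 |
| 5, 0.05 | 1.20 | 21.7 | 73% | 64% (8.4 df) | 7.3% | 32 |
| 6, 0.10 | 1.50 | 17.3 | 64% | 52% (6.7 df) | 10.7% | 39 |

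The last column keeps individual df; group-level df would ask for more.

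**Step 4: only the active arm clustered (sub-study 2 up to week 8).** The variance multiplier is the mean of the two arms, (1 + DE)/2.

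| m, ICC | Multiplier | Power, 50 df | Type I error if group ignored |
|---|---|---|---|
| 4, 0.02 | 1.03 | 80% (79.6%) | 5.3% |
| 5, 0.05 | 1.10 | 77% | 6.1% |
| 6, 0.10 | 1.25 | 72% | 7.8% |

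**Step 5: does over-recruitment cover it?** "To accommodate for up to a 20% drop-out, we will include 30 participants per treatment arm". If all 30 per arm are retained, power is 86.1% under independence. With both arms clustered and individual df it is 84% (m = 4, ICC 0.02), 79% (m = 5, ICC 0.05) or 70% (m = 6, ICC 0.10). If the full 20% drop out, 30 × 0.8 = 24 per arm remain, and power is 77.4% even without clustering.

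**The case against.** The case against has several parts, and much of it stands.

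- **The analysis.** A reader might infer that the trial will report standard errors that are too small. The article does not support that. It names a mixed model and is silent on random effects, which a condensed article commonly leaves to an analysis plan. The type I error figures apply only if the group is left out and the ICC is positive.
- **The unit of allocation.** A reader might infer that whole groups are randomised. The description of treatment in blocks points that way; allocation by age stratum points to individuals. If individuals are allocated, only correlation created by delivering treatment together remains, and it is likely smaller. It need not be zero, and the single oxygen level per room still ties a participant's allocation to the group he or she sits with.
- **The shared air.** It is tempting to say that breathing the same air makes outcomes correlated. Oxygen is controlled to within 0.1 percentage points of target, so the level is the arm effect itself and barely varies between sessions of one arm. Any correlation must come from period, staff and company.
- **The size of the ICC.** Desk dividers, individual iPads, adaptive training, outcome assessors who are absent from training, and a change-from-baseline outcome all speak for a small ICC. At the low end the loss is two to three points of power, and with all 30 per arm retained, m = 4 and ICC 0.05 still give 81%.
- **Sub-study 2.** The explicit sentence on group delivery concerns sub-study 1. Patients on treatment as usual receive no sessions before week 8, so at most one arm is clustered for the primary contrast.

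What the objection does not remove is the power statement. It is given in full, carries no allowance for grouping, and has less than one point to spare.

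**Conclusion.** The point holds in a limited form. Group delivery is stated for sub-study 1 and suggested for the active arm of sub-study 2. The claim of more than 80% power at 26 per group rests on an unstated assumption of practically zero within-group correlation.

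Under the assumed 4 to 6 per group and ICC 0.02 to 0.10, power in sub-study 1 is about 78% to 64%, or 72% to 52% with group-level degrees of freedom. In sub-study 2 it is about 80% to 72%. If the model omits the group, type I error is about 5.7% to 10.7% and 5.3% to 7.8% respectively. These ranges depend entirely on the assumed group size and ICC. That standard errors will in fact be too small, or that this is a cluster-randomised trial, is not established.

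**What to change.** 1. State whether individuals or treatment groups are allocated, how many people are treated together, and whether training and sham are mixed within a session.
2. Record a session-cohort identifier for every participant, including those already treated.
3. Include a random effect for cohort in the primary mixed model, with Kenward-Roger degrees of freedom. In sub-study 2 use a partially nested model with the cohort effect in the active arm only. Fix this before unblinding.
4. Restate power for the planned numbers over a stated range of ICC.

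The cost is one data field, one model term and a short addition to the power section; no participant procedure changes. The statistical price is real: wider intervals, a less favourable power figure, and few effective degrees of freedom for the oxygen contrast (about 7 to 11 at 26 per arm under the assumed group sizes). Recruitment was well advanced in April 2024, so the restated power will mainly serve to interpret the result.

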### Participants

For sub-study 1, we will recruit 120 healthy participants with no current or prior psychiatric illness. For sub-study 2, we will recruit 60 patients with affective disorders (MDD or BD) in partial or full remission (Hamilton Depression Rating Scale 17-items (HDRS-17; [43]) and the Young Mania Rating Scale (YMRS; [44]) score ≤ 14). Healthy participants are primarily recruited across the University of Copenhagen and other higher education facilities in Copenhagen to ensure that participants are able to take time off for the time-intensive study. Patients are mainly recruited through the Mental Health Services, Capital Region of Denmark, and through advertisements on relevant websites.

For sub-study 1, eligible participants are between 18 and 50 years of age, be fluent in Danish, and have no psychiatric history. For sub-study 2, patients are between age 18 and 65, be fluent in Danish, have a diagnosis of BD or MDD confirmed using the Schedules for Clinical Assessment in Neuropsychiatry (SCAN) [45], in partial or full remission (defined as a score of ≤ 14 on HDRS-17 and YMRS with objectively verified cognitive impairment according to Screen for Cognitive Impairment in Psychiatry (SCIP) [46] and/or self-reported cognitive impairment measured with Cognitive Complaints in Bipolar disorder Rating Assessment (COBRA) [47]. For SCIP, their performance must be > 0.5 standard deviations (SD) below their demographically adjusted expected total SCIP score or on minimum two SCIP subtest scores [48]. For COBRA, patients must report substantial cognitive impairment defined as a score ≥ 14 [47, 49]. We include a subjective measure of cognitive impairment as eligible patients can have suffered a cognitive decline from a high level of premorbid functioning, which may not be detectable by a cross-sectional evaluation with SCIP.

Common exclusion criteria for both sub-studies are schizophrenia or schizoaffective disorder, organic mental disorders (ICD-10 codes F00-09), history of neurological disorder (including dementia), alcohol or substance abuse, daily use of ≥ 22.5 mg oxazepam, or history of serious head trauma. To ensure safety, candidates are also excluded if they have previous altitude sickness, significant medical conditions (e.g., heart disease, diabetes, renal failure, untreated/insufficiently treated hypertension, and/or thrombosis), history of epilepsy or thromboembolic events, first-degree family with thromboembolic events before age 60, are pregnant or breastfeeding, currently take iron supplements, smoke, use other nicotine products regularly, or have a BMI > 30. All female participants who are not using hormonal contraceptives must take a pregnancy test before beginning the intervention to ensure that they are not pregnant. Participants are also excluded if they have received electroconvulsive therapy (ECT) three months prior to participation or are dyslexic. Regarding fMRI assessments, participants are not eligible if they suffer from claustrophobia and have a pacemaker and/or other metal implants inside their bodies. Participants are not eligible for PET assessments if they have participated in experiments with radioactivity (> 10 mSv) within the last year, have significant occupational exposure to radioactivity, or if they take medication incompatible with study aims (e.g., SV2A binding agents). Patients with mood disorders, who do not meet the fMRI and PET inclusion criteria, will not be excluded from the trial per se, but only from these neuroimaging assessments. All participants must provide written informed consent. The SPIRIT reporting guidelines were used for the current study [50]. See Appendix A for a completed SPIRIT checklist.

### Study setting

The ALTIBRAIN trial, including all neurocognitive assessments and intervention sessions, will be conducted at the NEAD (Neurocognition and Emotion in Affective Disorders) Centre, Department of Psychology, University of Copenhagen, and Psychiatric Center Copenhagen, Frederiksberg Hospital, Denmark. Furthermore, MR and PET scans are conducted at the Copenhagen University Hospital, Rigshospitalet, Copenhagen, Denmark.

### Randomization and blinding

Randomization is conducted in the database program REDCap [51], which is also used to store the collected data, utilizing a 1:1 allocation ratio. Randomization occurs after inclusion of the participants planned to undergo treatment sessions together. Treatment groups are stratified for age (> 27 in sub-study 1 of generally young volunteers/ > 35 in sub-study 2 of patients). For randomization purposes, date of birth is registered to determine the stratum to which the participant belongs at the time of enrolment. Study identification numbers are given consecutively within each stratum and treatment arm. Randomization is conducted in the randomization module in REDCap, where an un-blinded researcher inputs the stratum and the program then retrieves the allocated intervention. To ensure blinding of the outcome-assessors, the randomization module in REDCap is only accessible to the researchers, who are not involved in evaluation of the efficacy parameters.

Healthy participants in sub-study 1 are blind to the oxygen condition since the low/normal oxygen air blown into the room is of equal temperature and humidity. Furthermore, they are told that they receive one of two forms of cognitive training, which effectively blinded participants in a previous study [52]. After study completion, we will assess whether blinding has been maintained for each participant, since there is a small risk that some participants develop symptoms of mild altitude sickness which could unblind them to their intervention. Blinding of the outcome assessors is ensured by their absence during the training visits (where oxygen levels are displayed and monitored on a screen outside the room). Participants will be instructed not to disclose any information concerning their intervention during outcome assessments and under no circumstances will the allocation be revealed to the outcome assessors. The training visits are conducted by researchers who are not involved in outcome assessments.

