### Outcome measures

For an overview of outcome assessment domains, measures, frequency, and timing, see Table 1. The outcome measures listed below are consistent with the latest recommendations from the International Society for Bipolar Disorders (ISBD) Task Force [54].

**Table 1 Tab1:** Schedule of enrolment, interventions, and assessments

**Timepoint**	**Pre-intervention**	**Baseline (week 0)**	**Active treatment phase**	**End of treatment (week 4)**	**Follow-up (week 8)**	**Additional end of treatment assessment (week 12)** For sub-study 2 TAU group

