**Enrolment**						
Project information: written/oral communication	x					
Written informed consent	x					
Eligibility assessment	x					
Randomization	x					

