#### Primary outcome measure

The primary outcome measure is changes in a cognitive composite score, consisting of neuropsychological tests covering attention, memory, and executive functions from baseline to week 4. We have previously demonstrated an improvement on this *speed of complex cognitive processing* composite measure in patients with BD after 8 weeks of EPO treatment [28]. In the present trial, the specific tests included in the primary composite outcome measure are the Rey Auditory Verbal Learning Test (RAVLT) [55], The Repeatable Battery for the Assessment of Neuropsychological Status (RBANS) Coding [56], Verbal Fluency with the letter “D” [57], Wechsler Adult Intelligence Scale (WAIS)-III Letter-Number Sequencing [58], Trail Making Test Part B (TMT-B) [59], and Rapid Visual Information Processing (RVP) from the Cambridge Neuropsychological Test Automated Battery (CANTAB, Cambridge Cognition Ltd.). To derive the cognitive composite score, we will z-transform and sum performance scores from RAVLT total recall, TMT-B, WAIS-III Letter-Number Sequencing, RBANS Coding, Verbal Fluency (letter “D”), and RVP speed for correct responses [28].

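### In the open-label patient sub-study, Table 1 places randomization before baseline testing and nothing withholds the allocation, so patients may know their arm when the baseline of the primary change score is measured

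*Protocol article*

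**What the plan says.** Four places in the protocol article bear on the order of events in sub-study 2.

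- **Table 1, Enrolment block.** "Randomization" has a single mark, in the pre-intervention column, beside project information, consent and eligibility assessment. Baseline (week 0) is a separate column to its right. Every test that feeds the primary composite (RAVLT, TMT-B, Letter-Number Sequencing, RBANS Coding, verbal fluency, RVP) has its first mark in that baseline column.
- **Randomization and blinding.** "Randomization occurs after inclusion of the participants planned to undergo treatment sessions together". The trigger for allocation is inclusion of the session group. The sentence does not mention baseline testing.
- **Study design and procedure.** For sub-study 2: "Although patients will not be blinded to their allocated treatment arm, neurocognitive test results are generally not susceptible to placebo effects". The same paragraph says that blinded research assistants carry out the assessments.
- **Primary outcome measure.** The endpoint is change in a composite "covering attention, memory, and executive functions from baseline to week 4". Under Statistical analyses, the mixed model tests whether trajectories over time differ between groups.

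No section says when a patient is told the allocation, or that it is withheld until baseline testing is finished.

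**The concern.** The primary estimate in sub-study 2 is a difference between two changes, so the baseline measurement matters as much as the week 4 measurement. If patients know their arm at baseline, the two arms need not be comparable at that visit in effort, motivation or expectation, even though allocation was random.

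Early knowledge is plausible. The active arm has to plan 16 sessions of 3.5 hours over three weeks, while the treatment-as-usual arm waits until after week 8 for the intervention. Assessor blinding protects scoring and administration. It does not control how hard a patient tries.

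The point is specific to sub-study 2. Participants in sub-study 1 are blind to the oxygen condition and are told that they receive one of two forms of training.

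**Working it through.** **Order of events.** Table 1 does not treat its first two columns as interchangeable. Mood ratings and blood counts are marked in both, SCIP only in the first, and the cognitive tests first in the second. Read as printed, the schedule is eligibility and randomization, then baseline testing, then treatment. The text on randomization agrees with this, because it makes inclusion the condition for allocation.

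**How a baseline shift enters the estimate.** Let *d0* and *d4* be the differences (active minus control) in the composite at baseline and at week 4 that arise only because patients know their arm. Then

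bias in the difference in change = *d4* − *d0*.

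- If the effect exists only at baseline (*d4* = 0), the bias is −*d0*, the full shift with its sign reversed.
- If it persists unchanged (*d4* = *d0*), the bias is 0. If half persists, half remains.
- Lower baseline effort in the active arm (*d0* < 0) inflates the apparent benefit. Lower baseline effort in disappointed control patients (*d0* > 0) shrinks it.

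The direction therefore cannot be known in advance, and the two mechanisms may offset each other.

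**Inputs** (Sample size and power calculation): difference 0.4, SD of change 0.5, alpha 0.05, 26 per group. Sidedness is not stated for the primary outcome, so two-sided is assumed.

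**The plan's own figure.** For a two-sample *t*-test on change scores with *n* per arm, the noncentrality is λ = δ / (σ√(2/n)), with 2n − 2 degrees of freedom.

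- σ√(2/n) = 0.5 × √(2/26) = 0.1387
- λ = 0.4 / 0.1387 = 2.884 with 50 degrees of freedom
- Power = 0.807. With 25 per arm it is 0.791.

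So 26 is the smallest number per arm above 80%, and the stated figure reproduces.

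**Illustration.** The documents give no size for a shift. Assume an absolute shift *b* confined to baseline, on the same scale as the 0.4. For type I error, put δ = *b* into the formula (no true effect). For power when the shift runs against the intervention, put δ = 0.4 − *b*.

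| *b* (assumed) | Share of 0.4 | Two-sided type I error | Power if the shift runs against the intervention |
|---|---|---|---|
| 0 | 0% | 0.050 | 0.807 |
| 0.05 | 12.5% | 0.064 | 0.697 |
| 0.10 | 25% | 0.109 | 0.564 |
| 0.15 | 37.5% | 0.186 | 0.424 |
| 0.20 | 50% | 0.293 | 0.293 |

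The two entries in the last row agree because 0.4 − 0.2 = 0.2. Partial persistence moves a case up the table: a shift of 0.10 at baseline of which half remains at week 4 leaves a bias of 0.05 and a type I error of 0.064.

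**The case against.** The case for leaving the plan alone has several parts.

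- **The order rests on one table mark.** Randomization sits in an enrolment block, baseline is itself before the intervention, and the quoted sentence is silent on baseline testing. Fig. 1, the overview of events, was not available for this check. An article condenses a full protocol, and the moment of disclosure is an operational detail that may be settled there. This stands as a limit: the documents support that patients may know their arm at baseline, not that they do. It does not remove the point, because the schedule as printed permits it and the text does not correct it.
- **The protocol defends non-blinding.** It relies on blinded assessors and on the relative insensitivity of cognitive tests to placebo effects. The primary composite is wholly performance-based, the self-report scales are tertiary, and control patients are offered the intervention later, which should soften disappointment. These arguments reduce the likely size of a shift. However, the placebo argument concerns response to treatment, not effort at a baseline taken after allocation.
- **The size has no anchor.** This is correct. A reader might infer from the table that the false-positive rate in this trial is 11–29%. The documents do not support that: the shift is assumed, is taken to vanish by week 4, and may run either way.
- **Eligibility by COBRA.** A reader might also infer that some patients qualify only after being randomized, since Table 1 first marks COBRA at baseline while the Participants section makes it a route to entry ("For COBRA, patients must report substantial cognitive impairment defined as a score" at or above the cut-off). This does not follow. Participants makes a SCIP or COBRA result a condition of inclusion, and randomization comes after inclusion, so a qualifying score must already exist. Table 1 does not itemise every eligibility instrument; SCAN has no row either. At most, one screening mark is missing.

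**Conclusion.** The concern holds as a weakness in the order of procedures. Table 1 puts allocation ahead of baseline testing, the text ties allocation to inclusion, patients in sub-study 2 are not blinded, and nothing withholds the allocation. The baseline of the primary change score is therefore open to knowledge of the arm, and assessor blinding does not close that route.

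Bias is possible, not shown, and neither its size nor its direction is known. The figures for shifts of 0.1 to 0.2 are a worst case that rests on three assumptions: a shift of that size, confined to baseline, and a two-sided test with SD of change 0.5 and 26 per arm. No number stated in the plan is wrong on this point, and the sample size is unaffected. Adjusting for baseline in the analysis would not reliably remove a shift of this kind, because the covariate itself would be affected by allocation. This is a cheap improvement that should be made, not a fault that invalidates the trial.

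**What to change.** 1. For sub-study 2 patients still to be enrolled, complete the baseline cognitive, self-report and functioning measures before the REDCap allocation is drawn, or at least before it is disclosed to the patient.
2. Move randomization after baseline in Table 1, and reword the sentence in Randomization and blinding so that allocation follows completed baseline testing of the session group. If allocation is drawn earlier, state when it is disclosed. If practice already follows this order, the text and table corrections are all that is needed.
3. Report how many patients already enrolled knew their arm at baseline testing. The article gives 33 of 60 included as of April 2024, so the new order could reach at most 60 − 33 = 27 patients counted from that date, and the two procedures should be distinguishable in the report.
4. Optionally, add a COBRA screening mark to the pre-intervention column.

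The cost is a change in visit order and a table edit. The small downside is that session slots can be confirmed only once the whole group has finished baseline.
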